# 7. Outcomes

## 7.1 Primary outcome

## Pulmonary parenchymal fluid content measured by ReDS after 24 hours preceded by 10 minutes without oxygen-supplementation.

## 7.2 Secondary outcomes

1. Arterial blood gas concentration after 24 hours preceded by 10 minutes without oxygen-supplementation.
2. All-cause mortality at day 30
3. Days alive out-of-hospital to day 30
4. Time to freedom from oxygen-supplementation

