# 12. Statistical analyses plan

Baseline characteristics and outcomes of the patients in the groups will be compared individually. The primary exposure variable is allocation to the intervention group compared to control group. Categorical variables will be presented as numbers (frequencies) and compared with the Chi-Squared or the Fisher’s exact test, as appropriate, whereas continuous variables will be presented as mean ±SD if normally distributed, and as median (25^th^ percentile-75^th^ percentile) if non-normally distributed and compared with the T-test. In continues data, there are non-normally distributed, logarithmic transformation will be applied to approximate normal distribution as appropriate. Repeated measurements, mixed models will be made for analysis of the continuous variables with multiple measurements.

Missing data

In case of missingness greater than 5% for the primary endpoint, multiple imputations by chained equations will be applied as sensitivity analysis with generation of 10 individual data sets.

For other endpoints, first a worst case and best-case analysis will be made and if significant differences, multiple imputations will be performed.

Analysis of survival data and other outcomes

Kaplan-Meier curves for each group will be graphically displayed and compared by the log-rank test. Further multivariable Cox proportional hazard models will be applied to assess differences in time to death between treatment groups. These models will sequentially be adjusted for the interaction between treatment allocation, and each of the predefined covariates. Further, models stratified by individual components of the predefined covariates will be made as hypothesis generating. Any changes from the pre-specified analysis plan will be reported.

Outcomes will be evaluated using univariable and multivariable logistic regression models after examining assumptions of linearity and proportionality. Hazard ratios (HRs) and Odds ratios (ORs) with corresponding two-sided 95% confidence intervals (CI) will be presented.

Multivariable models are adjusted for:

*Admission SBP (quartiles), age, sex, body mass index, LVEF at admission (>50, 40-50, <40), NT-proBNP (above/below median), eGFR, supraventricular arrhythmia at admission, comorbidities (history of heart failure, obstructive pulmonary disease), systemic congested (Yes/no, defined as at least 3 kg above ideal weight at admission).*

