The covariates are pre specified before analyses and were chosen based on a consensus of the steering committee based on experiences from previous trials of AHF. Interaction between covariates will be tested by adding the interaction term to the models.

Subgroup analysis

Subgroup analysis will be made for all the prespecified covariates. Interaction with treatment effect will be tested for each covariate and a forest plot will be plotted.

Two-sided p-value of less than 0.05 is considered statistically significant. All analyses will be conducted in the modified intention-to-treat (ITT) (all randomized patients fulfilling the inclusion criteria and excluding those, which consent have been withdrawn) population. Statistical analyses are performed using the SAS statistical software, version 9.4 (SAS Institute, Cary, NC) and in R version 3.3.3 (R Foundation for Statistical Computing, Vienna, Austria).

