#### Data from emergency department (at the time of inclusion, T0)

- Weight in kg (measured in the ED)
- Time of symptom-onset
- Administered study-medicine
- Administered treatment prehospital
- Time of hospital arrival
- Time from hospital arrival to inclusion (calculated)
- Including site
- Blood gas analyses
- Echocardiography if available
- Vital signs at admission and after 1- and 6-hours including blood pressure, heart rate, respiratory rate, and peripheral oxygen saturation.
- Any concomitant therapy
- Routine biochemistry**
- ECG findings (Rhythm; signs of ischemia and QRS configuration: normal, STEMI, NSTEMI, LBBB, RBBB, other)

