# Appendix 4: study-related procedures

| Time | **Screening, baseline pre-randomization assessment** | **Randomization** | **12 h post randomization** | **24 h post randomization** | **Discharge** |
| --- | --- | --- | --- | --- | --- |
| Informed consent, patient | x |  |  |  |  |
| Demographics | x |  |  |  |  |
| Inclusion/ exclusion criteria | x |  |  |  |  |
| Medical history | x |  |  |  |  |
| Concomitant medications | x |  |  | x | x |
| Routine blood test | x |  |  | x (morning) |  |
| Arterial blood gas | x |  | x | x |  |
| ECG | x |  |  | x |  |
| Vital signs | x |  | x | x |  |
| Chest x-ray | x |  |  |  |  |
| Echocardiography | x |  |  | x |  |
| Focus lung-ultrasound | X |  |  | x |  |
| ReDS | X |  |  | X |  |
| Patient-dyspnea | X |  |  | X |  |
| Plasma volume | X |  |  | X |  |
| 5Q-DL |  |  |  |  | x |
| Adverse events reporting |  |  |  |  | x |

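### The two oxygenation-related secondary outcomes are planned without adjustment for oxygenation at entry, which gives up an inexpensive gain in precision or power

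*Protocol*

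**What the plan says.** Section 12 (Statistical analyses plan) assigns the t-test to continuous variables, with a log transformation where needed. One sentence adds mixed models for continuous variables measured more than once; it does not say how the baseline value enters. Cox models are named for time to death, and logistic models for outcomes in general. The adjustment list for the multivariable models follows these: "Admission SBP (quartiles), age, sex, body mass index, LVEF at admission (>50, 40-50, <40), NT-proBNP (above/below median), eGFR, supraventricular arrhythmia at admission", then "comorbidities (history of heart failure, obstructive pulmonary disease), systemic congested (Yes/no, defined as at least 3 kg above ideal weight at admission". That is 8 + 3 = 11 variables. The list is fixed: "The covariates are pre specified before analyses and were chosen based on a consensus of the steering committee". It also drives the subgroups: "Subgroup analysis will be made for all the prespecified covariates".

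Section 7.2 has four secondary outcomes. The first is "Arterial blood gas concentration after 24 hours preceded by 10 minutes without oxygen-supplementation"; the fourth is time to freedom from oxygen.

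Baseline oxygenation is collected. The Appendix 4 schedule marks "Arterial blood gas" at the pre-randomisation assessment, at 12 hours and at 24 hours. The T0 emergency-department list in section 12 (Data collection and management) includes "Blood gas analyses" and, among vital signs at admission, peripheral oxygen saturation. That list does not name the oxygen flow or FiO2 at the time of the baseline sample.

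**The concern.** The trial titrates oxygen, and two of its secondary outcomes describe how well oxygenation recovers. How hypoxaemic a patient was at entry plausibly predicts both. Entry is open to anyone with a saturation below 92% or a need of oxygen (section 6.3), so this severity can vary widely. A prognostic variable that is measured but left out of the analysis stays in the error term of a linear comparison. In a proportional-hazards comparison, leaving it out pulls the hazard ratio towards 1 and lowers power.

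What is at stake is efficiency in two secondary outcomes of a trial with 61 patients per arm. The validity of those comparisons is not in question.

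**Working it through.** **The plan's own figure.** For the primary outcome, with a difference of 4, SD 6.8, two-sided alpha 0.05 and power 90% (section 8), n per arm = 2 × (1.960 + 1.282)² × 6.8² / 4² = 60.7, so 61 per arm and 122 in total. The stated size is reproduced (power 90.1% by the normal approximation, 89.7% by the t-test). It does not depend on this point. The protocol gives no power figure for the secondary outcomes.

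**Which analysis applies to each outcome.**
- The 24-hour gas is continuous, so it falls under the t-test or the mixed-model sentence. The covariate list is attached to the Cox and logistic models and does not reach it. A mixed model with free group-by-time means leaves the 24-hour contrast unadjusted. One that constrains the arms to a common baseline mean would recover part of the loss, but the protocol does not specify it.
- Time to freedom from oxygen has no model of its own. If the Cox approach is carried over with the list, it still contains no oxygenation variable.

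**24-hour gas.** Let ρ be the correlation between the baseline and 24-hour values. The documents do not give it; 0.3 to 0.7 is assumed. Adjustment multiplies the residual variance by 1 − ρ². The equivalent unadjusted size is 61 / (1 − ρ²) per arm. Power is for an assumed difference of 0.5 SD, with unadjusted standard error √(2/61) = 0.181 SD.

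| ρ | 1 − ρ² | Equivalent n per arm | Power at 0.5 SD |
| --- | --- | --- | --- |
| 0 (unadjusted) | 1.00 | 61 | 78.9% |
| 0.3 | 0.91 | 67 | 82.5% |
| 0.5 | 0.75 | 81 | 89.0% |
| 0.7 | 0.51 | 120 | 97.2% |

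The fall in residual variance is therefore 9%, 25% or 49%.

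**Chance imbalance.** The standardised baseline difference between arms has SD 0.181, so the probability that it exceeds 0.25 SD in either direction is 2 × [1 − Φ(0.25/0.181)] = 16.7%. An imbalance of 0.25 SD shifts the unadjusted 24-hour difference by 0.25ρ, that is 0.075, 0.125 or 0.175 SD, less than one standard error. Given that imbalance, type I error is 5.9%, 7.2% or 8.2%. Averaged over all randomisations it stays at its nominal level: simulation of the unadjusted test (2,000 runs per setting) gave 4.1% to 5.6%.

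**Time to freedom from oxygen.** Simulation with 61 per arm, an assumed hazard ratio of 1.7, about 90% of patients with the event, and one prognostic covariate (600 runs per setting):

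| Log-HR per SD of covariate (assumed) | Power unadjusted | Power adjusted | HR estimated unadjusted |
| --- | --- | --- | --- |
| 0.3 | 72% | 77% | 1.64 |
| 0.5 | 66% | 79% | 1.59 |
| 0.7 | 56% | 77% | 1.51 |

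The small differences among the adjusted powers are within simulation error, about √(0.77 × 0.23/600) = 1.7 percentage points.

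**The case against.** The strongest reply is that the list was a steering-committee consensus drawn from earlier acute heart failure trials, that nothing in the protocol contradicts it, and that randomisation already makes the unadjusted tests valid. All of that stands.

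Three further objections limit the point.
- A reader might infer that the covariate list is what weakens the blood-gas analysis. The list is not attached to that outcome, and adding a variable to it would not by itself change a t-test or a mixed model.
- The gain for the gas is measured against an unadjusted linear model with an assumed correlation. The protocol allows oxygen freely before randomisation (section 5.1), whereas the 24-hour gas follows 10 minutes without it. PaO2 or SpO2 alone is then a weak measure of severity, and the true correlation may lie below the assumed range. If obstructive pulmonary disease, NT-proBNP, LVEF and the other listed variables were also in the model, the increment could be smaller again.
- The equivalent sample sizes are a linear-model result and cannot be carried over to time to freedom from oxygen.

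The objections leave the remedy standing. The baseline measurements are already scheduled, and the mixed-model sentence as written secures no adjustment for the gas and has no bearing on the time outcome.

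**Conclusion.** The point holds as a matter of efficiency in secondary outcomes 1 and 4. For the 24-hour gas the forgone gain is a 9% to 49% reduction in residual variance if the correlation is 0.3 to 0.7, and less if free oxygen at baseline weakens it. For time to freedom from oxygen it is about 5 to 21 percentage points of power under the simulated assumptions, with a less attenuated hazard ratio and not a smaller standard error. The adjusted hazard ratio is conditional on the covariate, so it is not the same quantity as the unadjusted one.

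A reader might go further and conclude that these comparisons are biased or invalid, or that the trial is undersized. The documents do not support that: overall type I error stays near 5%, and the primary outcome and the 122 patients are untouched. Nor is the lack of a subgroup by entry oxygenation an error. One more low-powered interaction test in 122 patients is a matter of preference.

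**What to change.** State the following before any unblinded analysis:

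1. Analyse the 24-hour blood gas by ANCOVA, with the corresponding baseline gas value as a continuous covariate together with the oxygen flow or FiO2 at that sample.
2. Analyse time to freedom from oxygen by a regression model adjusted for baseline oxygenation (continuous), again with the oxygen flow or FiO2 at the baseline sample.
3. Add a field for that flow or FiO2 beside the baseline gas on the T0 form. The automated device is set up only after randomisation (Appendix 2), so its record cannot be relied on for this value.

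The covariate list for the mortality models can stay as it is. A subgroup by entry oxygenation is optional and, if added, should be labelled exploratory. The cost is analysis-plan wording, one or two extra model terms and one form field. Fixing it in advance avoids a post hoc choice of covariate.

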# 8. Sample size calculations and statistical analysis plan

In a validation-trial of ReDS, Amir et al investigated 16 patients with acute heart failure and found a mean fluid content of 39.8 + 6.8 % [25]. Similar results were seen when estimating fluid content by the chest CT, which is regarded as the gold standard.

To have 90 % power to find a difference of 4 % in lung fluid content (change from 39.8% to 35.8%) with a standard deviation of 6.8, we need to include 122 patients (61 in each group). The α-level is 0.05, and the beta is 10%. We expect minimal dropouts. The study will include patients over an estimated period of 1 years in two centers. We will include patients until we have reached the estimated sample size without any missing values in the primary outcome, to ensure that we can conclude on our primary hypothesis.

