#### Remote Dielectric Sensing (ReDS)

Lung fluid content will be assessed noninvasively at admission and after 24 hours by the remote dielectric sensing (ReDS) device (Sensible Medical, Netanya, Israel). ReDS is an FDA-approved, wearable device developed by Sensible Medical Innovations that allows clinicians and other health care providers to quickly and accurately measure lung fluid in patients, noninvasively.

The lung fluid content is measured within the mid-region of the right lung. The measurement is presented as the percentage of the lung volume composed of fluid, (normal values for non-congested people is 20%-35% of fluid content) [25].

Using the ReDS technology in our study will seek to directly measure the degree of pulmonary congestion in acute heart failure patients and assess whether the effect of oxygen-level will be influenced by degree of pulmonary congestion at various points of care.

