#### Medical history characteristics (at the time of inclusion, T0)

- Age
- Sex
- Height in cm
- Weight in kg (usual weight)
- Previous New York Heart Association (NYHA) classification
- Comorbidity (Heart failure, AMI, arrhythmia, arterial hypertension, previous stroke, previous transitory cerebral ischemia, diabetes type I, diabetes type II, asthma or COPD, renal failure, liver cirrhosis, malignancy, alcohol abuse, drug abuse, HIV, AIDS, previous PCI, previous CABG, previous valve surgery)
- Medications
- Pervious LVEF
- Inclusion / exclusion criteria

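### The systemic-congestion covariate uses an undefined ideal weight as its reference; read literally, its subgroup result would largely reflect body size

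*Protocol*

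**What the plan says.** All references are to the protocol.

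- **Definition.** The adjustment list in section 12 (Statistical analyses plan) includes "systemic congested (Yes/no, defined as at least 3 kg above ideal weight at admission".
- **Neighbouring covariates.** The same list carries "age, sex, body mass index, LVEF at admission" and, as an indirect marker of cardiac filling, "NT-proBNP (above/below median". The systemic flag is the only covariate that is labelled as congestion.
- **Use.** Under the subgroup heading of section 12: "Subgroup analysis will be made for all the prespecified covariates". Each covariate also gets a test of interaction with treatment and a place in a forest plot. The Cox models take up the treatment-by-covariate interactions one after another.
- **Weights collected.** The data collection section lists height and "Weight in kg (usual weight" under medical history, and "Weight in kg (measured in the ED" under emergency department data. Neither list has an ideal weight.
- **A related aim.** Section 9, under Remote Dielectric Sensing, says that ReDS will be used to "assess whether the effect of oxygen-level will be influenced by degree of pulmonary congestion at various points of care". Appendix 4 schedules ReDS at baseline and at 24 hours, but admission ReDS is not in the section 12 list.

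**The concern.** A flag for systemic congestion should pick out patients who carry excess fluid. The natural reference is the patient's own weight without that fluid. An ideal weight is usually computed from height, and of the listed fields only height could supply one. On that reading an overweight patient with no fluid gain is called congested, and a lean patient who has gained several kilograms of fluid may not be.

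At stake is the interpretation of one prespecified interaction test and one forest-plot row. They would be reported as effect by systemic congestion while mostly separating heavier from lighter patients. In the adjusted models the flag would add little to BMI. At the least, two analysts working from the same database could derive different flags.

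**Working it through.** **1. The plan's own figure.** Section 8 plans for a "difference of 4 % in lung fluid content (change from 39.8% to 35.8" per cent, SD 6.8, two-sided alpha 0.05 and 90% power.
n per group = 2 × (1.960 + 1.282)² × 6.8² / 4² = 2 × 10.51 × 46.24 / 16 ≈ 60.7, rounded up to 61, so 122 in total. The stated size reproduces. It does not involve the congestion flag, so nothing below changes it.

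**2. The literal rule as a BMI cut-off.** If ideal weight is b × h² (b = ideal BMI, h = height in metres), then 3 kg or more over it means
admission BMI ≥ b + 3/h².
The protocol gives no b; 22 to 25 is an assumption.

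| Height (m) | 3/h² | Cut-off, b = 22 | Cut-off, b = 25 |
|---|---|---|---|
| 1.60 | 1.17 | 23.2 | 26.2 |
| 1.70 | 1.04 | 23.0 | 26.0 |
| 1.80 | 0.93 | 22.9 | 25.9 |

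The cut-off hardly moves with height, so the flag is essentially BMI cut in two.

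**3. Two constructed patients at 1.70 m (h² = 2.89).**
- Dry, BMI 29: weight 29 × 2.89 = 83.8 kg. Even with b = 25 the threshold is 25 × 2.89 + 3 = 75.3 kg. Flagged as congested with no fluid gain.
- Lean, usual weight 57.6 kg, 6 kg of fluid gained: weight 63.6 kg. With b = 22 the threshold is 22 × 2.89 + 3 = 66.6 kg. Not flagged.

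Measured against usual weight, the excesses are 0 kg and 6 kg, and both patients are classified correctly.

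**4. Share flagged, for illustration.** Assume admission BMI is normal with SD 5.5, and height is 1.70 m. Share = 1 − Φ((cut-off − mean)/5.5).

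| Mean BMI (assumed) | b = 22 | b = 25 |
|---|---|---|
| 26 | 70% | 50% |
| 28 | 82% | 64% |
| 30 | 90% | 76% |

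These are shares flagged, not shares misclassified.

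**5. How well the flag follows fluid gain.** A simulation of 400,000 patients per setting used assumed inputs only: height mean 1.70 m (SD 0.09); dry BMI mean 25, 27 or 29 (SD 4.5, 5, 5.5); independent fluid gain with mean 2 kg (SD 2) or 4 kg (SD 3), negative values set to zero; b = 22 or 25. Range over the 12 settings:

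| Quantity | Range |
|---|---|
| Flagged among those with gain under 3 kg | 45% to 88% |
| Flagged among those with gain of 3 kg or more | 54% to 93% |
| Difference between the two within a setting | 3 to 13 percentage points |
| Correlation of flag with gain of 3 kg or more | 0.05 to 0.13 |
| Correlation of flag with admission BMI | 0.57 to 0.80 |

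The two correlations are of different kinds and should not be compared directly. The within-setting difference in flag rates is the clearer measure: the flag barely separates patients with and without the fluid gain. For the BMI correlation the ceiling matters. A normal variable cut at a point that flags a share p correlates with its own cut version at φ(z)/√(p(1 − p)), where z is the cut point. That is √(2/π) = 0.80 at p = 0.50 and 0.162/0.286 = 0.57 at p = 0.91. The simulated values sit at about that ceiling, as step 2 implies.

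**The case against.** **The authors probably meant dry weight.** The label, the 3 kg margin, the words tying it to admission and the separate BMI covariate all point that way, and usual weight is collected. This is a fair reading, and it may be the intended one. But nothing in the protocol says so. If it is right, the wording is an undefined reference open to two readings, and the correction is the same.

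**Deriving a covariate is work for the SAP.** Often it is. Here, however, the protocol gives the definition itself and says that the covariates are prespecified. A later document would have to override the text, not complete it.

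**A reader might infer that the ReDS aim in section 9 rests on this flag.** It does not. That aim concerns pulmonary congestion and names ReDS as its measure, and the Background treats systemic congestion as something that may or may not accompany pulmonary congestion. The absence of admission ReDS from the list is a separate gap, which correcting the weight definition would not close.

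**A reader might infer that congestion is left uncontrolled and the treatment effect biased.** Allocation is randomised 1:1, so a poorly measured baseline covariate does not confound the comparison. It costs some precision. Overlap with BMI affects those two coefficients, not the treatment effect, and NT-proBNP carries some related information.

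**The percentages rest on assumptions.** This stands. BMI, height, fluid gain and ideal BMI are not in the document, so the figures show direction and plausible range, not the misclassification in this trial. Nor is the flag empty of information: fluid adds to admission weight, so it follows fluid gain weakly.

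**Conclusion.** The point holds in a limited form. The reference weight is undefined and uncollected. On the literal, height-based reading the flag is roughly a BMI threshold (22.9 to 26.2 for heights of 1.60 to 1.80 m, with ideal BMI assumed to be 22 to 25). Over the assumed range it separates patients with and without 3 kg of fluid gain by only 3 to 13 percentage points. The systemic-congestion interaction test and forest-plot row would then largely show effect by body size.

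The reach is secondary: the adjusted models and one subgroup row, in a section that itself calls its covariate-stratified models hypothesis generating. The 122-patient sample size, the unadjusted primary comparison and the validity of the overall treatment effect are untouched. It is worth correcting because the label would mislead a reader of the forest plot, and because the data for a better definition are already being collected.

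**What to change.** 1. **Redefine the flag in section 12:** systemic congestion is present if the weight measured in the emergency department exceeds the patient's usual weight, as recorded at inclusion, by 3 kg or more. Both fields are already on the data collection list.
2. **Separately, add admission ReDS as a continuous variable** to the prespecified covariate list and to the treatment-interaction tests. This gives the section 9 aim a listed analysis.

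Both are wording changes to make before the data are analysed. They need no new measurements and no more patients. The cost is that usual weight may be self-reported or missing in some patients. The number missing should be reported, and a height-based weight should not be put in its place.

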5.1 Detailed intervention and suggested initial treatment

Immediately after admission, the standard of care-treatment can be initiated as per discretion of the treating physician. Oxygen can be administered freely. The attending physician at the site will assess the patient’s eligibility for inclusion in the trial. After successful screening, the patient will be asked for written informed consent from study investigators. The sites will aim to obtain the consents as soon as possible. Patients will have nasal cannula or oxygen mask placed as the usual standard of care.

Patients will be screened and randomized in the emergency department to either liberal or restrictive oxygenation after providing informed written consent and oxygen is titrated to the prespecified target range using an automated feedback device (O2MATIC). Consented patients will be randomly allocated to study groups via the web-based system within REDCap. The allocation will be concealed. Time at randomization will be considered as study time zero (T0). All patients will receive usual standard of care except for their O2 management. The intervention will last for 24 h. After 24 h, patients will be switched over to usual care for oxygen therapy. We selected the 24 h time frame because in previous studies most patients with AHF were no longer on oxygen after 24 h [27]. If the treating physician thinks, that the patient need another oxygenation target and it is thought to be harmful to continue with the allocated target, the intervention-phase can be stopped prematurely.

Blinding

The intervention will be administrated double-blinded using the O2MATIC-device, which will titrate the oxygen-supplementation towards the intended target SpO2 without it being visible for patients, investigators or treating personnel. The robot will be programmed to deliver the intervention, record minute-by-minute data of oxygen-supplementation and SpO2. Furthermore, the robot will give an alarm if SpO2 drops below 88%. During the intervention-phase, SpO2 will not be measured by the nurses.

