## 9.2 Informed consent

The trial-protocol will be sent for approval by the ethics committee.

Consent will be obtained from the patient when he/she is deemed capable for the information and will be asked for a written informed consent (paper or in REDcap).

At any time, if the patient asks to be taken out of the trial, this will be respected. If a patient denies future participation in the trial, no additional data will be collected but all data collected up until the point of withdrawal will be included consistent with Danish law.

Information

Informed consent will include information that the hospital uses the best evidence-based therapy to relieve dyspnea for this patient. The patient is told that two equal treatment options exist, and we will give one of them after randomization, provided there are no contraindications or exclusion criteria. On the possible inclusion in the trial, every measure possible will be taken to ensure a quiet environment for the information.

Insurance

The patients in the study are covered by the Danish patient insurance.

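### The analysis set drops every randomised patient who withdraws consent, while the consent section says their data up to withdrawal will be included; the protocol does not reconcile the two

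*Protocol*

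**What the plan says.** Three parts of the protocol bear on this.

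- **Analysis population.** Section 12 (Statistical analyses plan), under the subgroup heading, assigns all analyses to one modified intention-to-treat population: "all randomized patients fulfilling the inclusion criteria and excluding those, which consent have been withdrawn". It does not distinguish withdrawal from treatment, withdrawal from follow-up, and refusal to let existing data be used.
- **Withdrawal.** Section 9.2 (Informed consent, printed within chapter 10) states: "At any time, if the patient asks to be taken out of the trial, this will be respected". For a patient who declines further participation, "no additional data will be collected but all data collected up until the point of withdrawal will be included consistent with Danish law".
- **Timing of consent.** Section 5.1 states: "Patients will be screened and randomized in the emergency department to either liberal or restrictive oxygenation after providing informed written consent". Appendix 2 gives the same order, with consent at step 2 and randomisation at step 4.

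Two rules on missing primary outcomes sit alongside. Section 8 says: "We will include patients until we have reached the estimated sample size without any missing values in the primary outcome". Section 12 adds: "In case of missingness greater than 5% for the primary endpoint, multiple imputations by chained equations will be applied as sensitivity analysis".

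**The concern.** The protocol gives two instructions for the same patient. Section 9.2 keeps what was collected before withdrawal; Section 12 takes the patient out of every analysis. Because Section 12 defines the only analysis population in the protocol, the choice between them affects the main result, and it could be made after data have been seen.

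Following Section 12 literally is also the weaker choice statistically. A randomised patient can withdraw only after allocation, so the exclusion rests on a post-randomisation event that may be related to how the patient has fared. Two kinds of information already in hand would be lost: the 24-hour ReDS value of a patient who withdraws between that reading and day 30, and that patient's observed time at risk up to withdrawal.

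**Working it through.** **1. The plan's own figure.** Inputs from Section 8: difference 4 points, SD 6.8, power 90%, α 0.05. Two-sided testing comes from Section 12 and 1:1 allocation from Section 4.

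n per arm = 2 × (1.960 + 1.282)² × 6.8² / 4² = 2 × 10.51 × 2.89 ≈ 60.7, rounded up to 61, so 122 in total. The stated figure reproduces. The exact t-test gives 61.7 per arm, with power 89.7% at 61, which is close enough. The sample size is not in question.

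**2. What each section does with a patient who withdraws.**

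| Time of withdrawal | Section 9.2 | Section 12 as written | What differs |
|---|---|---|---|
| Before the 24-hour reading | Primary outcome missing; earlier data kept | Patient removed | Baseline data and early time at risk; no primary value either way |
| After the reading, before day 30 | Primary value kept; follow-up known to withdrawal | Patient removed | A measured primary outcome and censorable follow-up |

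For the primary outcome, the two sections therefore differ in the values available only in the second row.

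**3. Time-to-event analyses.** No data are collected after withdrawal, so a withdrawn patient contributes only event-free time. Censoring keeps that time in the risk set; exclusion removes it. Removal can raise the Kaplan-Meier mortality estimate of that arm, or leave it unchanged, but cannot lower it. Day-30 vital status and days alive out of hospital remain incomplete for these patients under either section.

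**4. Possible shift in the primary difference.** The protocol gives no withdrawal rate and says only that few dropouts are expected, so the following inputs are assumptions. Let a fraction w of one arm, and none of the other, withdraw after the 24-hour reading. Let their mean differ by D from the rest of that arm. The full-arm mean is the mean of the rest plus w × D. Excluding the withdrawn patients therefore shifts the difference between arms by w × D.

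| w (one arm only) | D = 3.4 (0.5 SD) | D = 6.8 (1 SD) |
|---|---|---|
| 5% | 0.17 points (4% of 4) | 0.34 points (8.5%) |
| 10% | 0.34 points (8.5%) | 0.68 points (17%) |

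For scale, the standard error of the difference is 6.8 × √(2/61) = 1.23 points. The range runs from 0.17/1.23 = 0.14 to 0.68/1.23 = 0.55 standard errors.

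**5. Power.** If 122 were randomised and 2%, 5% or 10% of each arm were excluded without replacement, power would be 89.5%, 88.6% or 86.9% (normal approximation, 90.1% at 61 per arm). Section 8's continued recruitment would offset this for patients who have no reading. It does not say whether someone with a reading who is later excluded is also replaced. Replacement restores numbers but does not undo selective exclusion.

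**The case against.** The best defence is that the two sections can be read together. Section 9.2 does not say in what the data are included, so it might mean only that they stay in the trial database. Section 12 might have in mind only patients who refuse any use of their data. Either reading would remove the conflict. The protocol states neither, so the same clarification is needed whichever was meant. What stands is that this is an unreconciled conflict of wording, not proof that the two rules could never coexist.

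Several stronger readings are tempting, but the protocol does not support them.

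- **That every withdrawal costs a primary outcome.** The allocated target lasts 24 hours and the primary outcome is read at 24 hours. Someone who withdraws consent because of symptoms on the allocated target will mostly do so before the reading, and then has no primary value under either section. Those who withdraw later do so when oxygen is back to usual care, and a link to allocation is weaker.
- **That patients whose intervention is stopped early are removed.** Section 5.1 lets the treating physician end the intervention phase early. That is not withdrawal of consent, and Section 12 does not exclude those patients.
- **That the 30-day outcomes would be rescued.** Day-30 status and days alive out of hospital stay incomplete after withdrawal. The gain is limited to censored follow-up time.
- **That restricting the set to patients who meet the inclusion criteria is itself an error.** Those criteria are baseline features checked before randomisation, and Section 12 does not describe re-judging eligibility after outcomes are known. It is a debatable modified intention-to-treat choice.

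It is also fair to say that the shifts above come from a constructed one-sided scenario. Few or balanced withdrawals would give less.

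**Conclusion.** The point holds. For randomised patients who withdraw consent, Sections 9.2 and 12 say different things, and no other text settles which governs. Followed literally, Section 12 throws away 24-hour outcomes already measured in late withdrawers, and usable time at risk, for a reason arising after randomisation.

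Its size is limited. The 0.17 to 0.68 points rest on three assumptions: withdrawals in one arm only, 5% to 10% of that arm withdrawing after the reading, and values 0.5 to 1 SD away from the rest of the arm. Even the upper end is about half a standard error. Withdrawal before 24 hours is a missing-data problem that aligning the two sections does not solve. This should be fixed before analysis, mainly to close an open choice in the only analysis population defined. It does not show that the trial's result would be materially biased.

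**What to change.** Replace the definition in Section 12 (Statistical analyses plan) with wording that agrees with Section 9.2, for example: *All randomised patients are analysed in the group to which they were allocated. Patients who withdraw consent contribute all data collected up to withdrawal and are censored, or treated as missing, from then on. Only patients who refuse the use of data already collected are excluded; their number is reported by arm.*

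Under this wording, patients who withdraw before 24 hours stay in the set and count towards the 5% missingness threshold, but their outcomes still have to be handled by the missing-data methods.

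Optionally, if the inclusion-criteria condition is kept, state that eligibility is judged blind to allocation and outcome, from pre-randomisation data only.

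The cost is one sentence, or two with the option. No change to sample size or data collection is needed, and Section 9.2 already describes keeping the data as consistent with national law.
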